### 5.3.3 ECG

A 12-lead ECG will be made at visit 1, visit 2 (at time points as indicated in Table 5 in Appendix 2), visit 6 (at time points as indicated in Table 5 in Appendix 2) and visit 12.

The following parameters will be assessed: heart rate, PR-interval, QRS-interval, QT-interval, QT-c interval (Bazett). In addition, an assessment of abnormal morphology (rhythm, axis, P-wave, QRS complex, ST-T segment, T-wave) will be made.

### **5.3.4      Safety laboratory (routine biochemistry and hematology, coagulation, urinalysis, complement activation, inflammatory and immune response)**

#### **5.3.4.1      Routine biochemistry and hematology**

Routine biochemistry and hematology will be performed at visit 1, visit 1a, visit 2 prior to the first injection, visit 3, visit 4, visit 5, visit 6, visit 7, visit 9 and visit 12.

The parameters to be assessed for routine biochemistry and hematology are described in Appendix 3. There is no food restriction prior to blood sampling. The samples will be collected and processed according to standard hospital procedures and assessed by the local laboratory of the participating sites.

Special attention is required for the liver related enzymes in the clinical biochemistry assessments. A number of these liver enzymes (ASAT, ALAT and LDH) are also present in muscle and hence elevated levels are found in plasma (or serum) upon muscle damage, as in DMD patients. Indeed, these ASAT and ALAT findings in DMD patients have been found to correlate quantitatively with muscle specific CK levels in plasma (or serum) in DMD patients. Therefore, changes in ASAT and ALAT should be monitored in relation to CK for the evaluation of hepatotoxicity. If the changes in ASAT and ALAT levels (of over 3xULN) is disproportional to the CK changes, further evaluation is required. Dependent on the findings, this can include (i) further data analysis (e.g. graphical evaluation of trends in ALAT, ASAT and CK over time and compared to pre-treatment levels and/or regression analysis between ALAT/ASAT and CK levels for all samples of the patient), (ii) taking an additional confirmatory sample, (iii) starting more frequent monitoring and/or (iv) evaluating other alternative explanations. The sponsor should be notified of such concern. If deemed necessary, drug administration will be discontinued.

Other measures of hepatic and biliary function, including bilirubin,  $\gamma$ GT and ALP are not affected by the disease. However, ALP may be influenced by age (ALP from bone).

#### **5.3.4.2      Coagulation**

A blood sample for determining the aPTT will be collected at visit 2 and visit 6 at time points as described in Table 5 in Appendix 2. The samples will be collected and processed according to standard hospital procedures and assessed by the local laboratory of the participating sites.

#### **5.3.4.3      Urinalysis**

A midstream sample of urine is collected at visit 1, visit 1a, visit 2, visit 3, visit 4, visit 5, visit 6, visit 7, visit 9 and visit 12 in order to assess the urinalysis parameters (dipstick and quantitative) as described in Appendix 3.

The urine samples will be collected and processed according to standard hospital procedures and assessed by the local laboratory of the participating sites.

A 4 ml aliquot of all urine samples will be stored at  $\leq -60^{\circ}\text{C}$  in case future analysis is needed of other urinary markers of renal function in DMD patients.

#### **5.3.4.4      Complement activation**

Determination of complement activation by means of measuring complement split factors C3a, SC5b-9 and Bb will be performed at visit 2 and visit 6 at time points as described in Table 5 in Appendix 2. The collection, processing and shipping of these samples to the central laboratory will be described in the study specific laboratory manual.

#### **5.3.4.5      Inflammatory response**

Inflammatory response will be determined by measuring IL-6, TNF- $\alpha$  and MCP-1 at visit 2 and visit 6 at time points as described in Table 5 in Appendix 2. The collection, processing

and shipping of these samples to the central laboratory will be described in the study specific laboratory manual.

#### **5.3.4.6      Dystrophin antibodies in blood**

As DMD patients lack the dystrophin protein, it cannot entirely be excluded that a marked production of this protein by DMD patients may cause an immune response. It is not considered likely because spontaneous (natural) exon skipping occurs in DMD patients to some extent. This results in so-called revertant fibers expressing the (shortened) dystrophin protein. The frequency of such revertant fibers is generally far less than 1-2%, but nevertheless this could have been sufficient for immunological tolerance. This notion is supported by the absence of circulating antibodies to dystrophin in a study in *mdx* mice after induction of exon skipping and dystrophin protein expression by systemic application of oligoribonucleotides.

As an autoimmune response needs to develop over time and it is likely that antibodies will remain detectable for months, blood samples are only taken before administration, at the expected dystrophin peak levels and at the end of study. The assay is able to detect potential IgM and IgG antibodies against dystrophin. In case of a positive response, confirmation of specificity will be obtained by employing existing competing dystrophin antibodies.

For analytical methods refer to Appendix 4.

Formation of antibodies to dystrophin in blood will be determined at visit 2, visit 8 and visit 12. The collection, processing and shipping of these blood samples to the Prosensa laboratory will be described in the study specific laboratory manual.

#### **5.3.5      Adverse events**

The investigator will determine whether any AEs have occurred between visits. The subjects will be questioned using non leading questions and no specific symptoms will be suggested. Refer to Section 7 for further information on adverse event reporting.

#### **5.3.6      Local tolerability**

Local tolerability at the injection site(s) will be established by assessing the absence or presence and severity of erythema, edema, pain, increased temperature, induration and bruising on a scale of 0 to 3 where:

0= absent  
1= mild  
2= moderate  
3= severe

#### **5.3.7      Concomitant medication**

The investigator should record the use of all concomitant medications, both prescribed and over-the-counter, on the CRF. This includes drugs used on a chronic and as-needed basis. The following will be recorded on the CRF: name of medication, reason for taking concomitant medication, dose, unit, regimen, route of administration, start date and end date (if applicable).

### **5.4      Pharmacokinetic parameters during study period**

Phosphorothioate oligoribonucleotides distribute fast to tissues but remain stable with an expected terminal half life of approximately 4 weeks. This results in low plasma levels indicative of tissue redistribution at steady state. A sensitive ELISA has been set up that is able to measure such low plasma concentrations. This will allow the determination of trough plasma values and to determine overall tissue elimination rate for further evaluation of dose response relations.

Pharmacokinetic sampling will be done at all visits except visit 1 and visit 1a. Sampling has to be done prior to the administration of PRO051, and for visit 2 and visit 6 at time points as indicated in Table 5 (Appendix 2).

Per sample a volume of 0.6 ml venous blood will be collected to obtain at least 0.2 ml plasma. Samples will be taken from an intravenous cannula during the hospitalization visits and via venous puncture at the other visits.

Whole blood samples (0.6 ml) will be collected into EDTA tubes. After collection the samples should be centrifuged for 10 minutes at 1500G at 4°C. Plasma will be stored in screw cap polypropylene tubes and kept deeply frozen at -20°C until shipment.

At the Prosensa laboratory, PRO051 levels will be measured in plasma using GLP validated assay. For the analytical methods refer to Appendix 4.

## **5.5 Effect parameters during treatment beyond study period**

### **5.5.1 mRNA production and dystrophin expression in muscle biopsy**

A muscle biopsy taken from the tibialis anterior muscle will be taken at visit 37 and an optional muscle biopsy will be taken at visit 65 (week 52) or as soon as this protocol is implemented (Amendment 6) and convenient to the investigative site and subject. The optional muscle biopsy will be performed to track the effectiveness of PRO051 administration over a 12 month period. The muscle biopsy samples will be collected by open biopsy or with the conchotome method according to standard hospital procedures for obtaining muscle biopsies from children. The minimum amount of muscle tissue required is a small piece of muscle of AT LEAST 0.5 x 0.5 x 0.5 cm. The muscle tissue is immediately frozen in liquid nitrogen-cooled 2-methylbutane and stored at -80°C or -70°C till shipment. The collection, processing and shipment of these muscle biopsy samples to the Prosensa laboratory will be described in detail in the study specific laboratory manual.

The child can drink or eat normally before the procedure.

#### **5.5.1.1 mRNA production**

Endogenous production of the expected mRNA will be assessed at the Prosensa laboratory in muscle tissue collected via the muscle biopsy.

Small samples of the muscle biopsy will be stored for retrospective analysis. These will only be analysed in the event that any subject does not respond, to determine the reasons why. No additional material will be taken from the subjects.

Total muscle RNA will be isolated from muscle tissue sections and will be analyzed by RT-PCR^21.

RT-PCR analysis focusing on the area flanking the targeted exon 51 will be performed to detect specific exon 51 skipping in muscle. Depending on the subject's mutation different sets of DMD-gene specific RT and PCR primers will be used. Sequence analysis will be performed on isolated PCR products to confirm specific exon 51 skipping.

For analytical methods refer to Appendix 4.

#### **5.5.1.2 Dystrophin expression**

Dystrophin expression will be assessed at the Prosensa laboratory in the muscle biopsies by immunofluorescence analyses of cross-sections and by western blot analyses of total protein extracts.

For analytical methods refer to Appendix 4.

#### **5.5.1.3 Storage of muscle biopsy samples**

Muscle biopsy samples will be stored appropriately for potential scientific investigations in the future, with appropriate informed consent by the subjects and /or their parents/guardians. All

subjects have the right to change their mind regarding the use of stored samples for research at any time by notifying their doctor.

## **5.5.2 Muscle function**

### **5.5.2.1 Timed tests**

The timed tests consist of 10-meter walk/run test, timed rising from floor and stair climb. This combination of tests will be performed at selected visits. Refer to Tables 6 - 14 in Appendix 2 for exact time points, and refer to section 5.2.3.1 for execution instructions.

#### ***10-Meter walk/run test***

The subject will be asked to traverse a marked 10-meter measured walkway as quickly as he safely can. The 10-meter walk/run test should be performed preferably barefoot without shoes or orthoses. If not possible, testing can be done with shoes/orthoses and any use of shoes/orthoses should be documented. Time is recorded with stop watch from when his first foot crosses the start line till when the second foot crosses the finish line. If wall is touched, it should be noted how often. Care needs to be taken to ensure that the patient is safe when completing this test. The assessor can walk nearby to provide 'emergency' help should it be needed, but must not support or provide manual assistance for the patient in any way.

#### ***Timed rising from floor***

The subject will be told to stand up as quickly as possible from supine position with his arms by his side. The patient is allowed to use his arms for support while rising from the floor. Time is recorded with a stopwatch from the initiation of movement until the assumption of upright standing. The area should be free from furniture and the patient should not be wearing orthoses or using any aids.

#### ***Stair climb***

The subject will need to ascend four steps. Time is recorded with a stopwatch from the initiation of movement until the subject stands on the fourth step. If a flight of steps with handrail is available these should be used. If not, a box step (approximately 15cm high) should be used. A plinth or other immovable object may need to be available to provide support.

## **5.5.3 6-Minute walk test**

Subjects will be requested to walk for 6-minutes at selected visits, refer to Tables 6 - 14 in Appendix 2 for exact time points. The subject will be asked to walk at his own preferred speed up and down the fixed distance of 25 meters until they are told to stop after 6 minutes. The test should be performed preferably barefoot and without aid. If not possible, testing can be done with shoes/orthoses/aid and any use of shoes/orthoses/aid should be documented. The subjects are warned of the time and are told that they may stop earlier if they feel unable to continue. The total distance walked within 6 minutes (or until the subjects stopped in case of early termination of the test) will be collected in meters. In addition, the distance walked at 1, 2, 3, 4 and 5 minutes will be collected in meters. Also, the time needed to walk the distance of 25 meters is recorded for every 25 meter.

## **5.5.4 Muscle strength**

### **5.5.4.1 Handheld myometry**

The strength of the knee flexors, knee extensors, elbow flexors, elbow extensors, shoulder abductors and wrist dorsiflexors will be assessed at selected visits (Tables 6 - 14 in Appendix 2 indicate the exact time points), using a microFET dynamometer (Biometrics BV, Almere, the Netherlands).

### **5.5.4.2 Spirometry**

Spirometry will be done at selected visits, refer to Tables 6 - 14 in Appendix 2 for the exact time points. The following parameters will be assessed: FVC, FEV1, mouth pressure inhale, mouth pressure exhale, peak flow, peak cough flow.

### **5.5.4.3 Parent Questionnaire**

With the implementation of protocol Amendment 6, a short questionnaire will be completed by the subject's parents or legal guardian once every 6 months to capture the following:

- loss of any skills or daily activities
- improvements in daily activities
- development of new skills.

## **5.6 Safety parameters during treatment beyond study period**

### **5.6.1 Physical examination**

A full physical examination, weight, height and Body Mass Index will be assessed at selected visits, refer to Tables 6 - 14 in Appendix 2 for the exact time points. The following body systems will be examined: general appearance; ear, nose, throat; cardiovascular; pulmonary; gastrointestinal; urogenital; nervous system; musculoskeletal; extremities; dermatology; other.

Particular attention will be paid to the local tolerability at the site of the subcutaneous injections. Major events notable for disease progression that do not constitute an AE should also be noted on physical examination.

### **5.6.2 Vital signs**

At selected visits prior to study medication administration and at t=3hr after study medication administration (refer to Tables 6 - 14 in Appendix 2 for the exact time points), systolic and diastolic blood pressure, pulse rate and respiratory rate will be recorded after five minutes rest in semi-recumbent position.

Measures of blood pressure will be made using an automatic device. The same equipment will be used throughout the trial. Measurements will always be performed at the same arm.

### **5.6.3 ECG**

A 12-lead ECG will be made at selected visits, refer to Tables 6 - 14 in Appendix 2 for the exact time points.

The following parameters will be assessed: heart rate, PR-interval, QRS-interval, QT-interval, QT-c interval (Bazett). In addition, an assessment of abnormal morphology (rhythm, axis, P-wave, QRS complex, ST-T segment, T-wave) will be made.

### **5.6.4 Echocardiography**

An echocardiography will be made at selected visits, refer to Tables 6 - 14 in Appendix 2 for the exact time points.

The following parameters will be derived from M-mode measurements: left ventricular ejection fraction, fractional shortening, left ventricular posterior wall thickness, left ventricular septum wall thickness, left ventricular end-systolic diameter, left ventricular end-diastolic diameter, and left ventricular ejection fraction modified Simpson's.

### **5.6.5 Safety laboratory**

### **5.6.5.1      Routine biochemistry and hematology**

Routine biochemistry and hematology will be performed at selected visits, refer to Tables 6 - 14 in Appendix 2 for the exact time points.

The parameters to be assessed for routine biochemistry and hematology are described in Appendix 3. There is no food restriction prior to blood sampling. The samples will be collected and processed according to standard hospital procedures and assessed by the local laboratory of the participating sites.

Non-clinical studies with PRO051 suggest that it potentially may have hepatotoxic and nephrotoxic properties as it accumulates in the liver and kidney and is also associated with thrombocytopenia.

Therefore, monitoring of hepatic and renal function as well as thrombocyte count is of paramount importance. However, standard markers of hepatic and renal function may be confounded by the effects of DMD e.g. DMD subjects may have elevated ALAT, ASAT and CK levels (common markers of hepatic function) due to 'leaky' sarcolemmal membranes around muscle fibers, and serum and urinary creatinine concentrations (markers of renal function) may be variable due to changes in muscle mass. With this information in mind, the following parameters will be used for monitoring hepatic and renal function:

Hepatic function:      ALAT, ASAT, ALP, total bilirubin, bilirubin fractions (direct bilirubin),  $\gamma$ -GT, GLDH and LDH.

Renal function:      Urinalysis (including microscopy), serum and urine cystatin C, KIM-1, alpha-1-microglobulin and serum creatinine.

Urinalysis will be conducted on the first morning specimen after 8 hours of not drinking.

### **5.6.5.2      Thrombocyte Count**

Thrombocyte count will be performed on a two weekly basis during the treatment part of each 12 week cycle, and the following monitoring and discontinuation criteria apply:

- If thrombocytes are below the lower level of the normal range, thrombocytes will be checked prior to the next scheduled dose of study medication. Study medication will only be administered if thrombocytes are  $>75 \times 10^9/L$ ;
- If thrombocytes are still  $<75 \times 10^9/L$ , they will be checked on alternate days until they reach  $>100 \times 10^9/L$ ;
- If thrombocytes are  $<75 \times 10^9/L$ , study medication will be stopped and will only be considered for re-challenge should a clear alternative (non-drug related) cause be found after discussion between the Sponsor and Investigator;
- If the thrombocyte count has fallen  $>25\%$  from the previous count and is  $<100 \times 10^9/L$  then study medication should not be administered until thrombocytes return to  $>100 \times 10^9/L$ ;
- Investigators should be alert to trends for a consistent decrease in thrombocytes over two or more visits that may not meet the above criteria.

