All subjects will have an 8 week interruption to drug administration, following completion of Visit 85 (or as soon as Amendment 7 is approved after Visit 85). During the 8 weeks off drug, subjects will be asked to return for Visit 89 where safety parameters and efficacy measures will be made. Additional visits can be arranged depending on the current clinical status of the

subject and the clinical judgement of the investigator. Subjects will then re-start study administration according to a dosing regimen of;

- Subjects will receive one dose of 6 mg/kg PRO051 per week x 8 weeks if their body weight is  $\leq 50$  kg. This will be followed by 4 weeks off drug. This will continue in a cyclical manner.
- If a subjects body weight  $>50$  kg, he will receive one maximal dose of 300 mg PRO051 per week x 8 weeks This will be followed by 4 weeks off drug. This will continue in a cyclical manner.

Based on PK/PD modelling this regimen is predicted to result in an overall 12-week exposure that is somewhat lower than the continuous dosing regimen. The dystrophin levels are predicted to fluctuate between about 70% of the current level at the end of the off drug period, to about 80% at the end of the 8 weeks on drug. Although a compromise in efficacy is not anticipated, the impact on response will be closely monitored and if a perceived continuous decline in efficacy is observed, the investigator will discuss the potential benefit for an individual subject to return to continuous weekly dosing at 6mg/kg PRO051 with the Medical Monitor where the safety and tolerability is acceptable. The intermittent dosing regimen may, however, help to minimize organ burden from accumulation of this compound in organs, such as liver and kidney by allowing organs to washout during the off-treatment period. The overall risk benefit profile will be regularly assessed. Any change from intermittent dosing to continuous weekly dosing will be implemented at the start of a 12 week cycle.

The treatment with PRO051 beyond the study period should comply with the following conditions:

- Subject benefits from the PRO051 treatment
- Safety and effect assessments are performed as described in Appendix 2: Table 6, Table 7, Table 8 and Table 9.
- Maximum treatment period is until (whichever comes first):
  - the start of a next trial with PRO051 for which the subject is eligible, or
  - is exposed to safety risks outweighing potential benefits, or

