#### **5.6.5.10    Disseminated Intravascular Coagulation**

If either aPTT  $\geq 1.5 \times$  ULN, or thrombocytes  $< 75 \times 10^9$ /L or fibrinogen  $< 50\%$  of LLN are reached, the tests for fibrin split products and D-dimer should be performed. If fibrin split products and/or D-dimers are  $> \text{ULN}$ , and the aPTT or thrombocytes or fibrinogen remain outside of protocol limits as described above, study drug must be stopped and the subject should be immediately withdrawn from the study if not already discontinued. An elevated d-dimer or fibrin split products in the absence of aPTT  $> 1.5 \times$  ULN, or thrombocytes  $< 75 \times 10^9$ /L or fibrinogen  $< 50\%$  of LLN does not require stopping study drug unless it is associated with clinical signs or symptoms (e.g. bleeding).

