### **5.6.8 Laboratory Safety Parameter Stopping and Follow-up Criteria**

#### **5.6.8.1 Hepatic Toxicity**

Laboratory safety assessments including liver chemistries will be performed at selected visits, refer to Tables 6 - 14 in Appendix 2 for exact time points.

- ALAT  $\geq 8x$  ULN and total bilirubin  $2x$  ULN (plus  $>35\%$  'direct' bilirubin) or ALAT  $\geq 8x$  ULN and INR  $>1.5$ .
- $\gamma$ -GT  $>2x$  ULN and bilirubin  $2x$  ULN (plus  $>35\%$  'direct' bilirubin) or  $\gamma$ -GT  $>2x$  ULN and INR  $>1.5$

If a subject's results meet either of these criteria, the tests should be repeated immediately. If the results still meet these criteria, the study medication should be stopped until such time that the Sponsor (in discussion with the Investigator) considers that the benefit of further treatment with PRO051 outweighs the risk to the individual subject.

NOTE: if serum bilirubin fractionation is not immediately available, study medication should be discontinued if ALAT  $\geq 8x$  ULN and total bilirubin  $\geq 2x$  ULN. Serum bilirubin fractionation should be performed if testing is available. If testing is unavailable, record presence of detectable urinary bilirubin on dipstick, indicating direct bilirubin elevations and suggesting liver injury.

- ALAT  $\geq 8x$  ULN associated with symptoms of hepatitis (e.g. onset or worsening of nausea, anorexia, jaundice or abdominal pain) or hypersensitivity (fever, rash, eosinophilia).

If a subject's results meet this criterion, the test should be repeated immediately alongside a discussion with the Medical Monitor. Depending on the result of the re-test and general clinical picture, appropriate action with regards to discontinuing study medication will be decided between the Sponsor and Investigator.

Given the progressive and fatal nature of this disease, it is felt important that the hepatic stopping criteria allow the flexibility for the potential to re-start dosing in this subject population following an individual subject benefit: risk assessment.

However, if a subject's results meet the criterion below, the tests should be repeated immediately. If the results still meet this criterion, the study drug should be permanently stopped.

ALT  $>2x$  baseline values and bilirubin  $2x$  ULN (plus  $>35\%$  'direct' bilirubin) or ALT  $>2x$  baseline values and INR  $>1.5$ .

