| Adverse events                  | X                      | X     | X     | X     | X     | X     | X     | X     | X     | X     | X     | X     | X     | X     | X     | X     | X     | X     | X     | X     | X     | X     | X     | X     | X                           |
| Concomitant medication          | X                      | X     | X     | X     | X     | X     | X     | X     | X     | X     | X     | X     | X     | X     | X     | X     | X     | X     | X     | X     | X     | X     | X     | X     | X                           |

1. Other assessments to be performed prior to study medication administration unless specified otherwise

2. Vital signs include temperature, blood pressure, pulse and respiratory rate

3. Parameters will be derived from M-mode measurements and include left ventricular ejection fraction, fractional shortening, left ventricular posterior wall thickness, left ventricular septum wall thickness, left ventricular end systolic diameter, left ventricular end diastolic diameter, and left ventricular ejection fraction modified Simpson's

4. Collect a first morning urine specimen
5. Via finger prick
6. Timed tests consist of: 10-meter walk/run, rising from floor, stair climb
7. Parameters include FVC, FEV1, mouth pressure inhale, mouth pressure exhale, peak flow, peak cough flow
8. A DEXA scan may be performed at any visit, if deemed clinically necessary by the Investigator (i.e. rapid weight gain)
9. Prior to study medication administration
10. Adverse events to be obtained by weekly telephone call to parents by investigator / study nurse during off drug periods
11. Concomitant medication to be obtained by weekly telephone call to parents by investigator / study nurse during off drug periods

Table 10. Schedule of assessments for visits 110 – 133 (treatment beyond study period)

Subjects will not have to return to the hospital for laboratory safety testing during the 4-week treatment break UNLESS there is a medical / safety concern in which case the subject will be asked to return for further monitoring as determined by the investigator

| Visit                                        | 110                                                                                  | 111  | 112  | 113   | 114   | 115   | 116   | 117   | 118   | 119   | 120   | 121   | 122   | 123   | 124   | 125   | 126   | 127   | 128   | 129   | 130   | 131   | 132   | 133   | Withdrawal |

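### Section 5.6.5.2 fixes no repeat interval after a first thrombocyte count below 75 ×10⁹/L, because its alternate-day checks wait for a recheck tied to the next scheduled dose

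*Protocol*

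**What the plan says.** Section 5.6.5.2 of the Protocol schedules thrombocyte counts every two weeks, in the treatment part of each 12-week cycle only. Three of its bullets matter here.

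- **Bullet 1.** After a count below the normal range, "thrombocytes will be checked prior to the next scheduled dose of study medication". The dose is given only if the count is above 75 ×10⁹/L.
- **Bullet 2.** "If thrombocytes are still" below 75 ×10⁹/L, "they will be checked on alternate days until they reach" more than 100 ×10⁹/L.
- **Bullet 3.** A count below 75 ×10⁹/L stops study drug. Re-challenge is considered only if a clear cause other than the drug is found. No resampling time is given.

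The intermittent regimen, described under treatment beyond the study period, is eight weekly doses: "This will be followed by 4 weeks off drug". The notes above Tables 10 to 14 in Appendix 2 say: "Subjects will not have to return to the hospital for laboratory safety testing during the 4-week treatment break". They make an exception for a medical or safety concern, when the boy is asked back for monitoring that the investigator determines. Footnotes to Tables 9 to 14 keep weekly telephone calls going in off-drug periods.

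Section 5.6.5.10 adds that once thrombocytes are below 75 ×10⁹/L "the tests for fibrin split products and D-dimer should be performed". Withdrawal then depends partly on whether the abnormal value persists.

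**The concern.** The word *still* in bullet 2 refers back to the recheck in bullet 1, and that recheck has only one deadline, the next scheduled dose. A boy with a first count below 75 ×10⁹/L therefore has his drug stopped, but no rule says when he must be counted again. The authors evidently wanted alternate-day counts at this level. Their own trigger postpones them.

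The delay can be longest at the last dose of an intermittent cycle, because the next scheduled dose lies beyond the 4-week break and no count is scheduled in between. Entering the break does not end exposure: section 5.4 gives an "expected terminal half life of approximately 4 weeks". Section 5.6.5.1 associates the drug with thrombocytopenia and treats the thrombocyte count as one of the most important things to monitor.

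Some other stopping rules in the protocol do fix the repeat. For the main hepatic criteria (section 5.6.8.1), "the tests should be repeated immediately", with twice-weekly follow-up once the finding is confirmed. The first two inflammation criteria (section 5.6.5.5) also call for an immediate repeat.

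**Working it through.** The protocol states no recheck interval in days, so there is no figure to reproduce. The check is date arithmetic on the schedule tables.

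**Inputs**
- Recheck deadline: the next scheduled dose (section 5.6.5.2, bullet 1).
- Dosing interval: 7 days ± 1 day (Tables 10 to 14); Table 9 gives each visit a ± 1 day window.
- Table 9: last dose of a cycle at visit 101 (d+616), first dose of the next at visit 106 (d+651). Safety haematology, which includes the thrombocyte count (Appendix 3), is marked at both visits and at none between them.
- Table 10: the same pattern for visits 113 to 118 (w+100 to w+105) and 125 to 130 (w+112 to w+117).

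**Latest recheck that the text allows**
1. *Mid-cycle.* A low count at visit 119 is followed by a dose at visit 120: 1 week × 7 = **7 days**.
2. *Weekly dosing option (Tables 12 to 14).* There is no break, so the next dose is again **7 days** away.
3. *Last dose of an intermittent cycle.* Visits 101 to 106: 651 − 616 = **35 days**. Visits 113 to 118: (105 − 100) × 7 = 35 days. Visits 125 to 130: (117 − 112) × 7 = 35 days. The later cycle ends in Tables 11 to 14 give the same result. With ± 1 day at each end, the range is 35 − 2 = **33** to 35 + 2 = **37** days.
4. *After bullet 3 has stopped drug.* If no dose is scheduled, bullet 1 has no reference point and the recheck time is **undefined**, in mid-cycle as well as at cycle end.

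**Does another rule supply the interval?**

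| Provision | What it requires | Time or frequency for a repeat count |
|---|---|---|
| 5.6.5.2, bullet 3 | Stop drug below 75 | None |
| Notes above Tables 10 to 14 | Return if there is a safety concern | None; the investigator decides |
| Footnotes to Tables 9 to 14 | Weekly telephone call off drug | None; no blood count |
| 5.6.5.10 | Fibrin split products and D-dimer; a repeat count is implied | None |
| 6.4 | Sponsor and investigator discuss a stopped subject | None |
| 5.7 | PK sample when drug is interrupted | None |
| 4.5.2 | Final visit with haematology, if withdrawn | One visit; no interval |

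**With alternate-day checks from the first count below 75**

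The first repeat falls on day 2. If the count does not recover, the checks before the next dose are:
- mid-cycle, days 2, 4 and 6: 6 ÷ 2 = 3 counts;
- across a break, days 2, 4, …, 34: 34 ÷ 2 = 17 counts.

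**The case against.** The strongest reply is that no competent investigator would leave such a boy uncounted, and that the protocol gives several prompts to act. A count at the protocol's own stopping level is plainly a safety concern, so the recall clause in Tables 10 to 14 applies. Section 5.6.5.10 starts a coagulation work-up and cannot be completed without knowing whether the count has stayed low. Section 6.4 requires a discussion with the sponsor. Bullet 5 of section 5.6.5.2 asks for alertness to falling trends, and a scheduled count precedes each cycle-end count by two weeks (visit 123 before 125, for example). All of this stands and makes a long silent gap unlikely. It does not supply an interval.

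The comparison with other stopping rules is also uneven. The third inflammation criterion waits for more than two consecutive assessments, and the 24-hour urine test may be left until the next scheduled visit. The protocol does not always demand a prompt repeat.

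A reader might infer three stronger things that the documents do not support.
- *That the treatment break is unmonitored.* It is not: the recall clause and the weekly calls operate throughout.
- *That the recheck falls on day 35.* The requirement is for a count before the next dose, so 35 days is the latest literal time and an earlier count is allowed. Once drug is stopped, the time is undefined.
- *That the remaining drug, or the number of cycle ends in the schedule, measures the risk.* With a 28-day half-life, 0.5^(35/28) = 0.42 of the terminal-phase level remains at day 35, and Tables 9 to 14 contain 11 cycle-end counts (visits 101 to 221 in steps of 12). Nothing in the protocol links that residual level to platelet recovery. A boy stopped below 75 would not pass through all 11 visits, and weekly dosing removes the break for those who take it in Tables 12 to 14.

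**Conclusion.** The point holds as a minor drafting fault in a safety rule. After a first count below 75 ×10⁹/L the drug stop is clear, but no repeat interval is fixed. The trigger for alternate-day counts can defer them by up to 7 days in mid-cycle or on weekly dosing, and by up to 35 days (33 to 37) at the end of an intermittent cycle. The time is undefined where the stop leaves no next dose.

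This is more than missing detail, because the condition as written delays a safeguard that the protocol itself chose, and no other section sets a platelet interval.

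The conclusion rests on reading *still* as referring to the bullet 1 recheck, which is the natural reading of the two bullets in sequence. The documents give no frequency of counts below 75 ×10⁹/L, so the number of boys affected cannot be estimated. In practice the recall clause and the coagulation work-up would probably bring the count forward, which is why the point is rated minor.

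**What to change.** Reword bullet 2 of section 5.6.5.2 along these lines: *After any thrombocyte count <75 ×10⁹/L, on or off drug, repeat the count on alternate days, starting within 2 days, until it exceeds 100 ×10⁹/L.* This removes *still* and separates the follow-up from the dosing calendar.

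Add one sentence to bullet 1: *If a count from 75 ×10⁹/L up to the lower limit of normal occurs at the last dose of a cycle, recheck within 7 days.* Otherwise that group keeps the same cross-break deadline.

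The cost is two edits in the next amendment and some extra finger-prick counts, only in boys with a low count. For a count below 75, that is 3 before the next dose in mid-cycle and at most 17 before the next cycle, fewer if the count recovers. For a cycle-end count from 75 up to the lower limit of normal, it is one.
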